### **Assessment Methods For Full Sample**

Helminth infection will be assessed by fecal egg counts determined by quantitative formalin ether concentration technique. Presence and intensity of GI nematode infections will be assessed by the Formol ether method on a weighed amount of mixed feces ( $\approx 1$  g). The eggs present in the whole sediment will be counted in McMaster chambers except if very high numbers of a particular species is present, in which case a known proportion of the graduated slide will be counted.

Anemia will be assessed by hemoglobin concentration using the HemoCue method. When capillary blood samples are assessed (full sample protocol), the third drop of blood will be used. Severe anemia will be defined as hemoglobin  $< 7$  g/dL.

Malaria parasite density will be determined by counting parasites against leukocytes in a thick blood film, according to standard methods.

Anorexia will be assessed by maternal recall using established techniques.

PEM will be assessed by weight, length, and arm circumference-for-age following standard protocols.

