## 1. Study Protocol

### Aims Of The Project

**Aim 1:** To test whether community-based periodic treatment of children 6-23 months old with mebendazole will decrease rates of severe anemia and protein-energy malnutrition by at least 20%.

**Aim 2:** To determine whether young children infected with intestinal nematode infections exhibit a more pro-inflammatory response to nematode antigens (i.e. characteristic of T Helper 1 [Th1] cells) than age-matched uninfected children.

**Aim 3:** To test whether mebendazole treatment of infected children reverses this pro-inflammatory response.

**Aim 4:** To measure intestinal blood loss related to relatively light hookworm infection in young children, and whether intestinal blood loss is reduced after treatment with mebendazole.

**Aim 5:** To elucidate metabolic mechanisms that could explain the link between a pro-inflammatory cytokine response and anemia and protein-energy malnutrition. Specifically, we aim:

A) To determine whether newly infected children show defects in iron metabolism compared to age-matched uninfected children, in a manner consistent with mechanisms of the “anemia of chronic disease” (i.e. decreased iron absorption, decreased iron incorporation into erythrocytes, suppressed erythropoiesis, and/or shortened red cell life span);

B) To determine whether newly infected children catabolize protein at greater rates than age-matched uninfected children;

C) To determine whether newly infected children are more anorexic than age-matched uninfected children.

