## Experimental Design and Methods

We propose to conduct a community-based individually randomized trial of 3-monthly mebendazole treatment to assess the outcomes described in the framework and aims. The study area will be a geographically contiguous group of villages selected for the convenience of sample transport to the laboratory (within about 30 minutes drive by landrover). The PHL is currently conducting a complete population census of Pemba Island, which will allow us to define an area large enough to generate the needed sample size.

A representative sample of 2500 children ages 6-23 months will be screened for helminth infection. All 2500 children will be randomly allocated to treatment with a 3-day course of mebendazole, 100 mg twice daily, or identical placebo. This regimen was chosen to replicate the same drug used in our preliminary trial, but to maximize the efficacy of this drug against hookworms and *T. trichiura*. The study period will be 12 months duration, so that children have their first and final assessments in the same calendar month of the year, thus holding constant any seasonal effects. Anemia and PEM (**Aim 1**) will be assessed in the full sample.

To answer **Aims 2 & 3**, age-matched triplets of children will be selected according to their infection status at baseline. A triplet will be comprised of two infected and one uninfected child of similar age. The two infected children will be matched for species of infection. 250 matched triplets (total n=750) will comprise the Immunology Subsample. We chose 2:1 matching of infected to uninfected, because we are dealing with 3 species of infection and we want to increase our capacity to examine differences by species. Based on our preliminary data, a starting sample of 2500 children will be required to generate at least 500 infected cases. These children will be assessed for immunological parameters at baseline (prior to treatment) and again in the 10th month of the study, one month after the 4th (9-month) treatment round. The post-treatment time was chosen to maximize treatment effect by capturing all 4 rounds of treatment and by timing the assessment one month after the final treatment, when egg counts should be maximally reduced by the mebendazole.

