**Figure 2. Data collection schedule.**

| Study Month:                                    | 0 | 1 | 2 | 3 | 4 | 5 | 6 | 7 | 8 | 9 | 10 | 11 | 12 |
|-------------------------------------------------|---|---|---|---|---|---|---|---|---|---|----|----|----|
| FULL SAMPLE (n = 2500)                   |   |   |   |   |   |   |   |   |   |   |    |    |    |
| Fecal samples                                   | X |   |   |   |   |   |   |   |   |   |    |    | X  |
| Randomized Rx                                   | X |   |   | X |   |   | X |   |   | X |    |    | X  |
| Capillary blood                     | X |   |   | X |   |   | X |   |   | X |    |    | X  |
| Appetite                                        | X |   |   | X |   |   | X |   |   | X |    |    | X  |
| MUAC                                            | X |   |   | X |   |   | X |   |   | X |    |    | X  |
| Mother's milk                       | X |   |   |   |   |   |   |   |   |   |    |    |    |
| IMMUNOLOGY SUBSAMPLE (n=750) |   |   |   |   |   |   |   |   |   |   |    |    |    |
| Mother's fecal                                  | X |   |   |   |   |   |   |   |   |   | X  |    |    |
| Venous blood                        | X |   |   |   |   |   |   |   |   |   | X  |    |    |
| Anthropometry                                   | X |   |   |   |   |   |   |   |   |   | X  |    |    |
| HemoQuant                           | X |   |   |   |   |   |   |   |   |   | X  |    |    |

1) Capillary blood sample for determination of hemoglobin and malaria parasite density.

2) Only collected from mothers of children 6-12 months old.

3) Data collected in subsamples are in addition to the data collected for the full sample.

4) Venous blood sample will be used for assays of cytokine secretion in response to antigenic stimulation (whole blood assay), acute phase proteins, immunoglobulins, and iron status indicators.

5) HemoQuant assay will be performed on fecal samples collected for parasitology; no additional samples will be collected.

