### Justification Of Sample Size

Our starting point for the sample size calculation was the Immunology Subsample. The proposed starting sample size of about 750 children, after 15% attrition, provides 220 children per infection status group, randomly allocated into 2 treatment groups. Thus to compare treatment effects within infection groups, we plan to have about 110 children. Based on the ongoing work of Drs. [name], [name], and [name] in Nanjing China, where they are using the whole blood assay to assess cytokine responses to *Schistosoma mansoni*, 100 per group is a minimum number to detect important differences.

To generate this number of age-matched triplets for the Immunology Subsample, about 2500 children will need to be screened for infection. This will in fact be more than enough to address Aim 1. However, we propose to retain the entire group of 2500 children for several reasons. First, we want to retain the representative community-based sample to address Aim 1. The Immunology Subsample will be specifically constructed such that it is no longer representative of the community of young children. We want to make inference about the effects that would be observed if mebendazole treatment were provided to all young children in this environment, since screening for infection status would be impossible to implement in a public health program. Second, it has been our experience in Pemba that once community meetings have been held to inform and motivate participation in a research study, it is difficult to randomly select only some of the children into the actual study. Because participation in the study will confer some benefits to the study subjects and their communities, families resent being excluded from community-based studies. Third, the costs of implementing the Full Sample protocol are relatively small.

The sample size for the HemoQuant Subsample, 100 per infection intensity group, was based on our previous HemoQuant study of hookworm-related blood loss in Pemba school children. In that study we detected significant differences amongst infection intensity groups with 50 children per group, however, the spectrum of infection intensities in school children was much greater. Because infection intensities will be light in these young children, we have doubled our previous sample size to detect smaller blood losses.

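### Weight and length are promised for all 2500 children in the text, but Figure 2 schedules only MUAC for them and puts its one Anthropometry row in the non-representative Immunology Subsample, at months 0 and 10

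*Protocol*

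**What the plan says.** Aim 1 asks whether periodic mebendazole "will decrease rates of severe anemia and protein-energy malnutrition by at least 20"%. The section Experimental Design and Methods fixes the population: "Anemia and PEM (Aim 1) will be assessed in the full sample". Under Assessment Methods For Full Sample the measures are named: "PEM will be assessed by weight, length, and arm circumference-for-age".

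Figure 2 reads differently. Its full-sample panel (n = 2500) has rows for fecal samples, randomized treatment, capillary blood, appetite, MUAC and mother's milk. MUAC is marked at months 0, 3, 6, 9 and 12. No row covers weight, length or anthropometry. An Anthropometry row appears only in the Immunology Subsample panel (n = 750), at months 0 and 10. Footnote 3 adds: "Data collected in subsamples are in addition to the data collected for the full sample".

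Two further statements bear on this. Justification Of Sample Size says: "The Immunology Subsample will be specifically constructed such that it is no longer representative of the community of young children". It gives the wish to keep a representative sample for Aim 1 as the first reason for retaining all 2500 children. Experimental Design and Methods sets the study period at 12 months so that a child's first and last assessments fall in the same calendar month.

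**The concern.** The text and the schedule cannot both be followed. The text takes weight and length in every child; the schedule takes them, if at all, in 750. The only place where a weight or length method is described is the full-sample section. The additional methods for the Immunology Subsample describe no anthropometry, although that is where the schedule puts it.

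At stake are the weight and length indices in the population that Aim 1 is about. The Background opens with low weight-for-age as a risk factor for child death, and Table 1 reports WHZ < -1 among the pilot results that motivated the trial. Under Figure 2 neither would be available in the representative sample. The subsample values would also come from month 10, which loses the seasonal matching. No later analysis plan can repair this, because measurements not taken cannot be recovered.

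**Working it through.** **1. Text against schedule**

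| Item | Text | Figure 2 |
|---|---|---|
| Who has weight and length | Full sample, 2500 | No full-sample row; Anthropometry row in Immunology Subsample, 750 |
| Who has arm circumference | Full sample | Full sample |
| Last weight and length | Final assessment of a 12-month study | Month 10 |
| Last arm circumference | Same | Month 12 |

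Figure 2 does not define Anthropometry. Reading it as weight and length is an inference, supported by MUAC having its own row and by footnote 3, which makes the subsample rows extra to the full-sample rows.

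**2. How different the subsample is**

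- By construction it has two infected children to one uninfected: 500/750 = 67% infected.
- The protocol expects 2500 screened children to yield at least 500 infected: 500/2500 = 20%. This is a floor; the community share may be higher.

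**3. Illustrative power**

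The protocol gives no significance level, power or control rate for Aim 1, so there is no stated figure to reproduce.

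Inputs:
- Placebo rates from Table 1: WHZ < -1, 34.8%; MUAC < 13.5 cm, 22.0%.
- Relative risk 0.80, the reduction named in Aim 1.
- Assumed: two-sided alpha 0.05 and equal allocation.
- Attrition of 15%, which the protocol states only for the Immunology Subsample, is applied here to both samples.
- Children per arm: full sample 1250, or 1062 after loss; subsample 375, or 319 after loss.

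Formula, with p2 = 0.80 × p1 and p̄ = (p1 + p2)/2:

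power = Φ{ [ (p1 − p2)√n − 1.96 √(2p̄(1 − p̄)) ] / √(p1(1 − p1) + p2(1 − p2)) }

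For WHZ < -1: p1 = 0.348, p2 = 0.2784, p̄ = 0.3132; the two square-root terms are 0.656 and 0.654. With n = 319: (0.0696 × 17.86 − 1.96 × 0.656)/0.654 = (1.243 − 1.286)/0.654 = −0.065, so power is 47%.

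| Outcome, sample | No loss | 15% loss |
|---|---|---|
| WHZ < -1, full sample | 96% | 93% |
| WHZ < -1, subsample | 54% | 47% |
| MUAC < 13.5 cm, full sample | 79% | 72% |

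By the same formula, 80% power needs about 696 per arm for WHZ and 1287 per arm for MUAC.

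**4. Sensitivity**

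The control rates come from 99 placebo children aged 6–29 months. A simple 95% interval is p ± 1.96√(p(1 − p)/99).

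- WHZ: 34.8% gives 25% to 44%. Subsample power at 375 per arm then runs from 38% to 70%.
- MUAC: 22.0% gives 14% to 30%. Full-sample power at 1250 per arm then runs from 55% to 92%.
- If the relative risk in the subsample were 0.65, the pilot estimate for WHZ, subsample power would be 96% (93% after loss).

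**The case against.** A reader might infer that the wasting half of Aim 1 cannot be answered in the representative sample. The document does not support that. Aim 1 names protein-energy malnutrition, not weight-for-height. Arm circumference is one of the three listed measures, Table 1 reports MUAC < 13.5 cm under wasting malnutrition beside WHZ < -1, and Figure 2 schedules MUAC in all 2500 children at five visits, including month 12. This part of the objection stands: only the weight and length indices are lost.

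Figure 2 may also simply be incomplete. It departs from the text elsewhere: HemoQuant is shown at months 0 and 10, against pre-treatment and 1 and 12 months post-treatment in the text, and appetite is shown at month 9, which the text omits. Nothing shows a decision to drop weight and length, so this is an inconsistency between passages, and the harm arises only if the field follows the figure. That is fair, but no statement says which prevails.

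The power figures rest on assumptions, and an infection-enriched subsample could show a larger effect than RR 0.80. This also stands; the figures give scale only. Finally, randomization still protects treatment comparisons within the subsample. What would be lost is the target population, the timing and probably the precision.

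**Conclusion.** The contradiction is real and nothing in the protocol resolves it. If Figure 2 is followed, the arm-circumference form of the PEM question survives in all 2500 children, while weight-for-height, weight-for-age and length-for-age would be available only in a sample that is two-thirds infected by design, and only to month 10.

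Under the stated assumptions, power for WHZ < -1 roughly halves. The protocol's assurance that 2500 children more than suffice for Aim 1 would then not hold for WHZ, and would be doubtful for MUAC alone. The exact percentages should not be relied on. The finding itself rests on the mismatch between text and schedule, plus the well-supported but inferred reading of the Anthropometry row.

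**What to change.** Bring Figure 2 into line with Experimental Design and Methods and Assessment Methods For Full Sample: add a weight-and-length row to the full-sample panel at months 0 and 12. State in a footnote what the subsample's Anthropometry row contains. The cost is a brief extra measurement per child at two visits already scheduled.

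If weight and length will not be taken in everyone, amend both text sections so that MUAC is the Aim 1 PEM measure, label weight and length results as applying to the subsample only, and qualify the sufficiency statement in Justification Of Sample Size, with power shown over a range of control rates. This adds no fieldwork but narrows the malnutrition claim. Either change has to be made before baseline measurement begins.

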### **Additional Assessment Methods For Immunology Subsample**

Phlebotomy. Blood (5 mL sample) will be drawn at comparable times of the day into a vacutainer without anti-coagulant. 1 ml will be immediately dispensed into a sterile tube with heparin to be used in the whole blood assay (below). Additional drops will be used to make blood films for total leukocyte and reticulocyte counts, and malariometry. The remaining 2 ml will be allowed to clot and serum will be collected.

Whole Blood Assay to evaluate T cell responses. This assay will be carried out as described previously. Cells will be stimulated with worm antigens (*Trichuris*, hookworm or *Ascaris*); the mitogen, PHA; and purified protein derivative (PPD) of *Mycobacterium tuberculosis*. PPD has been chosen as a positive control antigen as BCG vaccination is given at birth. Supernatants will be harvested at appropriate times for measurement of Interleukin (IL-) 4, 5, 6, 10, 13, TNF- $\alpha$  and IFN- $\gamma$ . Optimum harvesting time for each cytokine to the antigens will be defined in the study population in project year 1. Cytokines will be measured by quantitative ELISA using commercially available antibody pairs and recombinant cytokine standards (Pharmingen). To control for interplate variation, a positive control supernatant from bulk PHA or LPS stimulated cultures will be used on all plates. IL-4, IL-13, and IL-5 have been chosen as indicators of activation of Th2 type responses, each of which also plays a defined role in the protective immune response against helminth infections. IL-10 is implicated in the suppression of IFN- $\gamma$  mediated Th1 responses, for example in the early response to *S. mansoni* infection in humans. IFN- $\gamma$  has been chosen as a measure of Th1 activation, and for its important role in the induction of TNF- $\alpha$ .

TNF- $\alpha$  and IL-6 are proinflammatory cytokines (which induce acute phase proteins) produced by macrophages following their activation by IFN- $\gamma$ . TNF- $\alpha$  may play a direct role in regulating Th2 responses to helminths, and has a direct effect on cachexia and wasting. All of these cytokines have been measured in whole blood cultures using the techniques developed by [name] et al. (1999 and unpublished) and by others. The utility of measuring cytokine responses in the peripheral blood as an indicator of responses elsewhere in the body has recently been confirmed. Antigens for the whole blood assay will be prepared as follows. Trichuris, hookworm and Ascaris adult worms will be recovered by Quantrel (pyrantel/oxantel) treatment of children and adults in the areas in which the main study will be carried out. Worms will be frozen at  $-70^{\circ}\text{C}$  and antigen prepared in culture medium by sonication and centrifugation. Protein will be estimated and the antigen concentration optimized for use in the WBA and specific antibody ELISAs.

Serum acute phase proteins. Inflammation will be assessed by ELISA assay of serum C-reactive protein (CRP),  $\alpha$ -1-anti-trypsin ( $\alpha$ -1-AT), ferritin and eosinophil cationic protein (ECP) in venous samples. CRP and  $\alpha$ -1-AT are acute phase proteins known to suppress erythropoiesis, ferritin is both an iron storage protein and a positive acute phase protein, and ECP is a marker of eosinophil activity that is elevated in helminth infections. CRP and  $\alpha$ -1-AT will be assessed by in-house ELISA assay systems based on enzyme-labelled (CRP) and biotinylated ( $\alpha$ -1-AT) purified proteins. Ferritin will be measured using the commercial kit made by Ramco, Inc. We will develop an ELISA system for assaying ECP following Reimert et al.

Antibody detection. Total IgE, a marker of established infections with many species of helminth, will be measured using the Pharmacia ImmunoCap method. Isotype-specific antibody responses will be assessed by ELISA for IgG, IgG1 (associated with Th1 responses), IgG4 and IgE (both associated with Th2 responses) against hookworm, Ascaris, and Trichuris antigens. The contribution of maternal-derived antibody to that measured in the children's sera may be uncertain but the data will be valuable in conjunction with information on infection presence and intensity.

Iron status will be assessed by measurement of erythrocyte protoporphyrin in a drop of whole blood using a digital hematofluorometer (Aviv Biomedical). Serum ferritin and transferrin receptor will also be measured and will be considered as iron status indicators. However, our prior experience in young Pemban children suggests that serum ferritin mainly reflects the acute phase response, and that transferrin receptor mainly reflects erythropoiesis in this population. In contrast, erythrocyte protoporphyrin was relatively specific to iron deficiency.

Erythropoiesis will be assessed according to the model of Beguin, which evaluates erythropoietin concentration, transferrin receptor concentrations and reticulocyte index relative to hemoglobin concentration. Erythropoietin and transferrin receptor concentrations will be measured using commercial ELISA kits. Reticulocyte counts will be made on thin blood films examined microscopically.

Morbidity in the week prior to each immunology assessment will be assessed by maternal recall using local terms for acute symptoms.

#### **Additional Assessment Methods For HemoQuant Subsample**

Intestinal bleeding will be assessed by the HemoQuant assay. This assay measures the quantity of heme excreted per gram of feces. In subjects who consume little red meat intake (like young Pemban children), this is an accurate measure of intestinal blood loss.

#### **Additional Assessment Methods For Metabolic Subsample**

The sequence of the metabolic studies is shown in Table 3. Protein catabolism, iron absorption and iron incorporation into red cells will be assessed before mebendazole treatment. Pre-treatment measures in newly infected and uninfected children will allow us to test cross-sectionally for

metabolic changes associated with new infections. We will also assess body composition and plasma volume. This is necessary to estimate body pool sizes, which may differ from normal assumptions because of the chronic mild malnutrition and subclinical infections in Pemban children. One month post-treatment we will reassess protein catabolism, and assess red cell survival rates. Post-treatment values will allow us to assess whether mebendazole reduces protein catabolism or alters red cell life span.

**Figure 3. Summary of metabolic studies**

|                                           | Time relative to mebendazole treatment     |                                                                |                                       |
|-------------------------------------------|--------------------------------------------|----------------------------------------------------------------|---------------------------------------|
|                                           | 2 weeks pre-treatment                      | On day of treatment                                            | 1 month post-treatment                |
| Iron metabolism                    | Administration of iron isotopes            | Assessment of iron absorption and incorporation into red cells | Assessment of red cell survival       |
| Protein catabolism                 | Pre-treatment protein turnover study       |                                                                | Post-treatment protein turnover study |
| Body composition and plasma volume | Isotopic dilution; Sodium bromide dilution |                                                                |                                       |

General procedures. Infants will be brought to an outpatient clinical facility at the Pemba PHL accompanied by an adult relative. The atmosphere will be designed to provide comfort and entertainment for the infants, mothers and any siblings who come along. A medical doctor will be present throughout every protocol, which will be implemented by experienced pediatric nurses. Appropriate incentives will be given to families who participate to compensate their time and inconvenience.

Iron metabolism protocol. Iron absorption and red cell iron incorporation will be measured by administering oral ( $^{57}\text{Fe}$ ) and intravenous ( $^{58}\text{Fe}$ ) stable iron isotopes to each infant. Blood samples will be taken 2 weeks post-dosing to measure the enrichment of these tracers in red blood cells. The enrichment of isotopes in this sample will allow us to measure both iron absorption and the degree of red cell iron incorporation. An additional blood sample will be taken 4 weeks post-treatment to measure potential differences in the rate of erythropoiesis or red cell destruction between infection groups in children treated with placebo (i.e. newly infected vs. uninfected, n=10 per group) or between treatment groups in newly infected children (n=10 per group).

At the 2-week pre-treatment visit, each infant will be given an oral dose of NaBr (1.5 g/kg) and  $^{57}\text{Fe}$  (7 mg, as ferrous sulfate). Infants will then be allowed to nurse and will be fed a standard meal 1 hour post-dosing. The majority of prior studies in infants have estimated red blood cell iron incorporation at 90% in infants. This assumption simplifies the studies and allows them to be done using only a single oral iron isotope. However, the degree of iron incorporation into red cells may be altered in these infants due to subclinical infections. We will therefore directly measure the degree of iron incorporation into red cells by administering a second intravenous iron isotope. An intravenous dose of  $^{58}\text{Fe}$  (0.6 mg as ferrous citrate) will be administered over 5 minutes. Blood volume assumptions are also necessary. Most studies estimate blood volume at 65-80 mL/kg. Information obtained from the deuterium (body composition study, see below) and NaBr tracer dosing will allow us to directly measure extracellular fluid volume and total body water and reduces the assumptions necessary for making calculations about iron metabolism. A venous blood sample will be taken 4 hours after the oral dosing to measure NaBr concentration.

At the treatment visit, a 5 mL blood sample will be drawn by venipuncture. One mL whole blood will be digested using ultrapure acids. Iron will be extracted using cation-exchange chromatography. The eluent will be dried and the iron residue will be dissolved in nitric acid. Iron isotope ratios will be determined using magnetic sector thermal ionization mass spectrometry (Finnigan MAT 261, Bremen, FRG). These methods have been previously described in detail.

Few data have addressed the impact of parasitic infections on the lifespan of erythrocytes in infants and the timing of maximal iron incorporation into red cells. Studies have indicated that the lifespan of the erythrocyte is markedly lower in infants than adults and a recent study has found alterations in the time course of iron incorporation into erythrocytes in infants. An additional blood sample is already planned at the 1 month post-treatment visit for immunology and protein turnover studies. We will also analyze the enrichment of iron isotopes in these blood samples to compare the stability of the tracer enrichments between infection and treatment groups.

Protein turnover study. Protein catabolism will be assessed by measuring oxidation of leucine, an indispensable amino acid, labelled with a stable tracer. The fraction of leucine flux that is oxidized is constant under normal conditions, but increases markedly with protein breakdown. The protocol consists of two sequential oral tracer infusions: (1) Measurement of CO2 production: bicarbonate tracer (CO3NaH (99% APE, Cambridge Isotopes, MA) will be administered as a priming oral dose of 0.4 mg/kg, followed by a 3-hour constant oral infusion of 0.4 mg/kg/hr, administered in three equal aliquots every 20 minutes. (2) Measurement of leucine oxidation: upon completion of the bicarbonate infusion, the leucine tracer infusion will start. L-[1-C]-Leucine (95% APE, Cambridge Isotopes, MA) will be administered as a priming dose of 2 mg/kg, followed by a 4-hour constant oral infusion of 2 mg/kg/hr for 4 hours. Doses will be given in 20-minute aliquots. During the infusion study children will be fed at hourly intervals. Intake of breast milk will be determined by test weighing. Feeding will approximate the pro-rated calculated 24-hour energy requirement for actual weight. Breath air (15 mL) will be sampled for isotopic enrichment by asking the child to blow into a small balloon.

Body composition study. Body composition will be determined by isotopic dilution, using deuterium oxide. A fixed, 20 g oral dose of H2O (99.5APE, Cambridge Isotopes, MA) will be administered at the pre-treatment visit at the same time the NaBr is given. Saliva samples will be collected at 3 and 3.5 hours post-dose, for measurement of isotopic enrichments.

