To answer **Aim 4**, a subsample of 300 children will be constructed of hookworm-negative (n=100), light hookworm infections (1-999 epg, n=100) and moderate hookworm infections ( $\geq 1000$  epg, n=100). These classifications are lower than typically used in school children, and were chosen for children 6-24 month who have lighter infection intensities but whose total body iron store is limited or absent. Therefore small quantities of GI blood loss could have significantly alter their iron balance. Intestinal blood loss will be measured in this subsample at just prior to treatment, and 1 and 12 months post-treatment. This HemoQuant subsample will be drawn from the Immunology Subsample, so that immunologic data will also be available.

To answer **Aims 5A and 5B**, a subsample of 20 newly-infected and 20 uninfected (total n=40) children will be selected from the Immunology Subsample. This number, although small for an epidemiologic study, is large for a metabolic study involving stable isotopes. To our knowledge it is the largest sample size ever involved in a similar protocol. However, many factors may affect the metabolism of these children and it is essential to limit the heterogeneity within this sample to reduce variance unrelated to the factors of interest (i.e. helminth infection status and cytokine response). Thus, we will impose inclusion criteria based on age (12-23 months old), wasting malnutrition (weight-for-height Z scores  $\geq -1$ ), recent illness (no significant morbidity in the prior 2

weeks, and malaria infection (<1000 parasites/mL). Because these children will be drawn from the age-matched triplets defined for the Immunology study, the 20 children in the newly-infected group and the uninfected groups will be further matched on age within the 1-year-old age category.

**Specific Aim 5C** will be addressed using maternal reports of poor appetite, a method that is valid and very simple to implement. Therefore anorexia will be assessed in the full sample of 2500 children just prior to treatment and at 3, 6 and 12 months post-treatment.

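### The oral sodium bromide dose of 1.5 g/kg, read as salt, is 10.5-16.5 g per toddler: too large for a dilution marker, so it must be verified before anyone is dosed

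*Protocol*

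**What the plan says.** The dose stands in the Protocol under Additional Assessment Methods For Metabolic Subsample, in the iron metabolism protocol: "each infant will be given an oral dose of NaBr (1.5 g/kg". It is stated once. No strength, volume, cap or reference goes with it, and no other section restates or qualifies it.

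The purpose is measurement. The same section says that "the deuterium (body composition study, see below) and NaBr tracer dosing will allow us to directly measure extracellular fluid volume and total body water", and Figure 3 lists the method as "Isotopic dilution; Sodium bromide dilution". The reading comes from one later sample: "A venous blood sample will be taken 4 hours after the oral dosing to measure NaBr concentration". The deuterium oxide, a fixed 20 g, "will be administered at the pre-treatment visit at the same time the NaBr is given".

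The recipients are "a subsample of 20 newly-infected and 20 uninfected (total n=40) children", restricted to ages 12-23 months (Experimental Design and Methods).

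**The concern.** A dilution marker works only if it leaves the space it measures essentially unchanged. Sodium bromide is an osmotically active salt, and a gram-per-kilogram amount is not a trace quantity.

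Two things are at stake:

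- **Safety.** Staff who prepared the dose as written would give each toddler more than 10 g of salt, with no therapeutic purpose.
- **Measurement.** If the figure is literal, the 4-hour sample would reflect an extracellular space that the marker itself had enlarged. That volume is meant to reduce the assumptions behind the Aim 5A iron calculations.

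Gram scale alone is not the fault. The deuterium oxide is also given in grams, but it is water and behaves quite differently, as the working shows.

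**Working it through.** **From the Protocol:** 1.5 g/kg NaBr; 40 children; age 12-23 months; sample at 4 hours; 20 g deuterium oxide; other tracer doses as listed in step 5.

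**Assumed, because the Protocol gives no values:** body weight 7-11 kg; total body water T = 0.55-0.65 L/kg; extracellular volume E = 0.25-0.45 L/kg; baseline osmolality 285 mOsm/L; complete absorption, full osmotic equilibration, and no excretion or water intake before sampling. The molar mass of NaBr is 102.9 g/mol and the density of deuterium oxide is taken as 1.105 g/mL.

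**1. Dose per child.** 1.5 × 7 = 10.5 g; 1.5 × 11 = 16.5 g.

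**2. Molar and osmotic load.** 1500 mg/kg ÷ 102.9 = 14.58 mmol/kg each of sodium and bromide. Two ions give 29.16 mOsm/kg.

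**3. Concentrations.**
- Bromide before any water shift: 14.58 ÷ 0.45 = 32.4 mmol/L to 14.58 ÷ 0.25 = 58.3 mmol/L.
- Osmolality rise: 29.16 ÷ 0.65 = 44.9 to 29.16 ÷ 0.55 = 53.0 mOsm/L, which is 16-19% of 285. This does not depend on E.

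**4. Expansion of the extracellular space.** Keep the salt outside the cells and let water move until osmolality is equal throughout:

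new E = T × (285E + 29.16) ÷ (285T + 29.16)

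| T (L/kg) | E (L/kg) | Change in E |
|---|---|---|
| 0.65 | 0.25 | +21.8% |
| 0.55 | 0.25 | +18.8% |
| 0.65 | 0.35 | +11.7% |
| 0.55 | 0.35 | +9.0% |
| 0.65 | 0.45 | +6.0% |
| 0.55 | 0.45 | +3.5% |

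With half the dose absorbed (14.58 mOsm/kg), osmolality rises by 22.4-26.5 mOsm/L and E by 1.9-11.7%.

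**5. Comparison with the other tracers in the Protocol.**
- Deuterium oxide: 20 g is 20 ÷ 11 = 1.8 to 20 ÷ 7 = 2.9 g/kg. Its volume is 20 ÷ 1.105 = 18.1 mL, which adds 0.25% (11 kg, T = 0.65) to 0.47% (7 kg, T = 0.55) to body water and carries no salt.
- Leucine: 2 + 2 × 4 = 10 mg/kg in total.
- Bicarbonate: 0.4 + 0.4 × 3 = 1.6 mg/kg in total.

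The last two are read as isotopic enrichment, so they do not indicate what the bromide dose should be. They show only that nothing nearby supports a salt load in grams per kg.

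**6. How far the possible readings diverge (illustration only).** If the figure meant grams of a solution, an assumed strength of 1-5% would give 15-75 mg/kg of salt, 20 to 100 times less than the literal reading. At T = 0.60 L/kg the osmolality rise would then be about 0.5-2.4 mOsm/L. A slip from mg to g would mean 1.5 mg/kg, or 10.5-16.5 mg per child.

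**The case against.** The strongest reply is that the document contains no contradiction. The Protocol calculates nothing from 1.5 g/kg, gives no competing dose and sets no tolerable load. If grams of a dilute solution were meant, the text is incomplete rather than wrong, and the strength might be in a laboratory procedure that is not shown. That reading remains possible. But the text names NaBr and no solution, so the dose cannot be prepared safely from it under either reading.

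A second reply is that the fluid volumes, weights and absorption are all assumed, and that the no-intake assumption does not match the visit: the Protocol lets the child nurse and provides a meal one hour after dosing. This stands in part. The 45-53 mOsm/L is an upper estimate, and the expansion range is wide, with a modest lower end. Intake would lower osmolality, though, without undoing the expansion, and the rise stays above 20 mOsm/L even at half absorption.

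Third, the effect on Aim 5A is not quantified. Both infection groups receive the same dose per kg, so part of the error would be shared. The Protocol's remark that "Most studies estimate blood volume at 65-80 mL/kg" spans about ±10% around its midpoint (7.5 ÷ 72.5), but that is a different compartment and serves only as a sense of scale. The objection is fair, and it makes the measurement argument secondary to safety.

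Finally, a physician attends every session and experienced paediatric nurses carry out the procedures. That lowers the chance of harm but does not correct the written dose.

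**Conclusion.** The concern holds. As a mass of salt, 1.5 g/kg is incompatible with use as a dilution marker and is a safety hazard: 10.5-16.5 g per child at 7-11 kg, and an osmolality rise of 45-53 mOsm/L if fully absorbed with no intake or excretion. The exact figures rest on the assumed weights, fluid volumes and absorption. The conclusion that the load is far too large survives the whole range examined.

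The intended dose cannot be recovered from the document. The measurement bias follows only if the figure is literal, and its effect on the comparison of infected with uninfected children is unknown. The scope is the 40-child metabolic substudy; Aim 1, sample size and error rates are unaffected. Because the consequence is physical harm to toddlers, this must be corrected before the substudy starts.

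**What to change.** Give no child sodium bromide at 1.5 g/kg of salt until the clinical and pharmacy team has verified the figure against its source. Then amend the iron metabolism protocol to state the dose as mass of NaBr salt per kg body weight, with the strength if a solution is meant, at a level shown not to change the extracellular space materially. I propose no replacement dose, since the document gives no basis for one.

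The cost is one pharmacy check and a one-line correction. Visits, samples and sample size do not change.
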